### Follow-up

Outcome data will be extracted from the medical record after participants are discharged from hospital, reach a corrected gestational age of 40 weeks or die (whichever happens first). The research assistant will also assess participants on at least a weekly basis to maintain contact with nursing staff, discuss any protocol violations, monitor for adverse events, and address any other issues that arise. Nursing staff will also be instructed to submit possible adverse events to the research assistant as soon as they occur. These include any cases of rectal bleeding, rectal perforation, and anal fissure.

### Outcomes

Outcomes for the external pilot study will be recruitment rate (i.e., percentage of eligible infants randomized), completion rate (i.e., percentage of infants reaching the primary endpoint of full enteral feeds), and treatment-related adverse events (i.e., safety outcomes). The pilot study will also allow us to better estimate the explicit cost per infant of conducting a randomized trial on this topic (i.e., considering the total costs of database design, data storage, printed materials, and salary for research assistants). We will also assess the frequency and type of protocol violations and post-randomization exclusions.

The primary outcome for the multicenter trial will be time in days to full enteral feeding (defined as 150 mL/kg/day). Advancing the rate of enteral feeds is typically based on a standardized NICU feeding protocol [24–26]. Deviations from this protocol occur when infants become unwell, develop signs of feeding intolerance, or if there are other clinical concerns. Secondary outcomes will include feeding volume on day 14 of life (in mL/kg), days to complete meconium evacuation, days of parenteral nutrition, incidence of NEC, incidence of line sepsis, compliance with treatment regimen, and mortality.

### Sample size

For the external pilot study, we hope to recruit 30 participants (15 per group) over a 6-month period. Previous reviews recommend using at least 12 participants per group, and some indicated that a total sample size of 30 may be more appropriate [27–29].

### Potential pitfalls

Adherence to the study protocol was a serious issue in a randomized controlled trial of glycerin enemas from Austria [14]. This may have occurred because some clinicians did not believe in the efficacy of glycerin enemas and tended to withhold this intervention among participants in the therapeutic arm. This will be less of an issue in our trial since glycerin suppositories are commonly used in the NICU at McMaster Children’s Hospital and are much less invasive.

Another issue to consider is post-randomization withdrawals or exclusions. While this is an issue in any randomized controlled trial, this will present a unique challenge in our study since participants will have been alive for less than 48 h when they are enrolled. Some infants may not have had prenatal screening and serious congenital anomalies that would have excluded them from the study may not be diagnosed until days or weeks after randomization. Even in cases of excellent prenatal care, some conditions (e.g., Hirschsprung’s disease) cannot be diagnosed until the postnatal period [30, 31]. The best way to handle this will be to follow all randomized participants to the primary endpoint of full enteral feeds and analyze the data on the basis of intention-to-treat.

Losing participants to follow-up is unlikely to occur since all premature infants are monitored in hospital until they are tolerating full enteral feeds and reach 37 weeks corrected gestational age. Some participants who are doing well clinically may be transferred to a NICU in a community hospital that is not part of this study, but this is unlikely to occur until after these infants have reached full enteral feeds. Finally, the mortality rate in this population is approximately 10 % [32, 33]. While our exclusion criteria will exclude most of the infants at risk for postnatal mortality, some participants may die before they are randomized, complete the treatment regimen, or reach full enteral feeds.

### Statistical analysis

Frequencies and 95 % confidence intervals using normal approximation will be used to estimate recruitment rate and percentage infants reaching the primary endpoint. We will also report the rate of protocol violations, post-randomization exclusions, and incidence of adverse events related to the study intervention. We will also report the mean cost per infant randomized. All data will be analyzed in the Statistics Package for the Social Sciences (SPSS) [34].

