### Duration of treatment

Infants enrolled in this trial will receive active treatment or placebo once daily until meconium evacuation is complete. This will be defined as two bowel movements free of meconium staining. Previous studies have demonstrated that this process takes approximately 6 to 9 days [14]. The study intervention will be withheld and reassessed daily in cases of thrombocytopenia (platelet count < 100 × 10^9^/L), suspected coagulopathy (bleeding from any orifice, confirmed coagulopathy (international normalized ratio >1.4, partial thromboplastin time >39 s, fibrinogen <1.00 g/L, thrombocytopenia (platelet count <100 × 10^9^/L), or neutropenia (absolute neutrophil count <0.5×10^9^/L).

The study intervention will be stopped early in cases of clinical deterioration (vasopressors, prostaglandins, culture-proven sepsis, NEC, or death) or treatment-related adverse events (rectal bleeding, rectal perforation, or anal fissure). Previous trials of glycerin suppositories and enemas did not report single case of rectal bleeding, rectal perforation, or anal fissure [14–16]. As such, the risk of these events occurring in the current study is low.

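### The normal-approximation 95% interval fixed for the completion rate is unreliable with 30 infants if completion is about 90% or more, as the protocol implies

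*Protocol article*

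**What the plan says.** The Statistical analysis section fixes the interval method for two pilot outcomes: 95% "confidence intervals using normal approximation will be used to estimate recruitment rate and percentage infants reaching the primary endpoint". It names no other method for small counts or for proportions close to 0 or 100%.

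The second of these is a named pilot outcome. The Outcomes section lists the "completion rate (i.e., percentage of infants reaching the primary endpoint of full enteral feeds".

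Under Sample size, "we hope to recruit 30 participants (15 per group) over a 6-month period". Under Potential pitfalls, the plan is to "follow all randomized participants to the primary endpoint of full enteral feeds and analyze the data on the basis of intention-to-treat", so the denominator for completion stays at about 30.

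The article gives no expected completion rate. Potential pitfalls does bear on it:
- "Losing participants to follow-up is unlikely to occur since all premature infants are monitored in hospital until they are tolerating full enteral feeds".
- Transfer to a community hospital is described as unlikely before full feeds.
- Mortality in this population is put at approximately 10%.
- It adds that "our exclusion criteria will exclude most of the infants at risk for postnatal mortality".

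**The concern.** The usual normal-approximation (Wald) interval takes the observed proportion plus or minus 1.96 estimated standard errors. Near 100% in a small sample, two things go wrong. The interval is symmetric although the sampling distribution is skewed, so the upper limit can pass 100%. The estimated standard error also shrinks towards zero as the observed proportion approaches one, so the interval becomes too short when the result looks best.

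If about 10% of infants die in the source population, most of those at risk are excluded, and few are lost or transferred early, then about three or fewer of 30 would fail to reach full feeds. That is where the method breaks down. At stake is whether the reported range for a named feasibility outcome can be read as a 95% interval. Its lower end matters most, since that is the pessimistic figure a reader would carry into planning the multicenter trial.

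**Working it through.** **Inputs.** Two-sided 95% level, so z = 1.96 (Statistical analysis). n = 30 (Sample size), with all randomized infants kept (Potential pitfalls). The true completion rate p is an assumption; values from 0.80 to 0.98 were checked. The article states no interval or expected rate, so there is no figure of its own to reproduce.

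**Step 1: limits for x completers out of 30.** With p̂ = x/n:
- Wald: p̂ ± z·√(p̂(1−p̂)/n).
- Wilson: [p̂ + z²/2n ± z·√(p̂(1−p̂)/n + z²/4n²)] / (1 + z²/n).

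Example, 27/30: standard error = √(0.9 × 0.1/30) = 0.0548. Wald gives 0.900 ± 1.96 × 0.0548 = 0.793 to 1.007.

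| Result | Wald | Wilson | Clopper-Pearson |
|---|---|---|---|
| 26/30 | 74.5–98.8% | 70.3–94.7% | 69.3–96.2% |
| 27/30 | 79.3–100.7% | 74.4–96.5% | 73.5–97.9% |
| 28/30 | 84.4–102.3% | 78.7–98.2% | 77.9–99.2% |
| 29/30 | 90.2–103.1% | 83.3–99.4% | 82.8–99.9% |
| 30/30 | 100–100% | 88.6–100% | 88.4–100% |

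The Wald lower limit exceeds the Wilson one by 4.9 points at 27/30 (79.3 − 74.4), 6.9 points at 29/30 (90.2 − 83.3) and 11.4 points at 30/30 (100 − 88.6).

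**Step 2: how often this happens.** Every result of 27 or more gives an upper limit above 100% or zero width. With X distributed as Binomial(30, p):

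| True p | P(X ≥ 27) | of which zero width, p³⁰ |
|---|---|---|
| 0.80 | 12% | 0.1% |
| 0.85 | 32% | 0.8% |
| 0.90 | 65% | 4% |
| 0.95 | 94% | 21% |
| 0.97 | 99% | 40% |

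**Step 3: actual coverage.** Coverage at p is the sum of Binomial(30, p) probabilities over the results whose interval contains p.

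| True p | Wald coverage | Misses with lower limit above p | Wilson coverage |
|---|---|---|---|
| 0.80 | 94.6% | 4.4% | 96.4% |
| 0.85 | 94.2% | 4.8% | 96.5% |
| 0.87 | 90.4% | 8.4% | 95.1% |
| 0.90 | 80.9% | 18.4% | 97.4% |
| 0.91 | 93.7% | 5.9% | 95.2% |
| 0.92 | 91.0% | 8.2% | 97.1% |
| 0.93 | 88.3% | 11.3% | 94.5% |
| 0.95 | 78.2% | 21.5% | 93.9% |
| 0.97 | 59.7% | 40.1% | 94.0% |

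A 95% interval with equal tails would put 2.5% in the third column. The jump between 0.90 and 0.91 has a simple cause. The lower limit at 29/30 is 90.2%, so 29/30 misses a true rate of 0.90 but covers 0.91. From 0.91 upward, almost all misses come from 30/30 alone.

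**Step 4: the recruitment rate.** About 150 eligible infants a year (Setting) gives about 75 in 6 months. If 30 of 75 are randomized, Wald gives 28.9–51.1% and Wilson 29.7–51.3%. Wald coverage at p = 0.40 with n = 75 is 94.0%, so the planned method is acceptable there.

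**The case against.** The strongest reply is that the article never says completion will be 90% or more. The only figure it gives is population mortality, and some of its text points downward. Anomalies such as Hirschsprung's disease may be found after randomization, and those infants stay in the analysis. Data capture ends at discharge, 40 weeks corrected age or death, so some infants may not reach full feeds in time. The Discussion reports an earlier trial in which 3/25 per group were transferred before complete outcomes were obtained. At a true rate of 0.85 the Wald interval does its job. This stands as a limit on the point. It does not remove it, because the same section of the article calls loss to follow-up and early transfer unlikely, which makes a high rate the fair reading.

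One may also say that truncating at 100% makes the limits presentable. It hides the impossible upper limit but leaves the lower limit too high and 30/30 at zero width. Nor does it help that the Wilson interval also derives from a normal approximation: the article does not name it, and the phrase ordinarily means Wald.

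Several stronger readings are tempting but not supported:
- *Coverage is poor throughout 90–100%.* It is not: 93.7% at 0.91 and 91.0% at 0.92.
- *A zero-width interval is the likely result.* It needs 30/30, with probability 4% at 0.90 and 21% at 0.95.
- *The feasibility decision is compromised.* The article ties no progression threshold, test or sample size to this interval. The frequency is reported too, so a reader can recompute the limits.
- *The safety reporting is also wrong.* Earlier trials "did not report single case of rectal bleeding, rectal perforation, or anal fissure", so a zero count is likely, and the article plans an incidence without mentioning an interval. But it does not exclude limits or reporting by arm, and an article may leave that detail to the full plan. The same applies to intervals for protocol violations and post-randomization exclusions.

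**Conclusion.** The point holds for the completion rate. The plan commits to a method that, over most of the range its own statements imply, does not deliver the stated 95% coverage: 81% at a true rate of 0.90, 78% at 0.95 and 60% at 0.97. It more often than not produces an upper limit above 100% or no width at all (65% at 0.90, 94% at 0.95). The error runs almost wholly in one direction, towards a lower limit that is too favourable.

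This rests on three assumptions: that the phrase means the Wald interval, that the denominator is 30, and that completion is about 90% or more, which is inferred. If the true rate is 0.85 or lower, the planned interval is adequate. Severity is modest, since the estimate is descriptive.

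**What to change.** In Statistical analysis, for the percentage of infants reaching full enteral feeds, replace the normal approximation with the Wilson score method (or Clopper-Pearson, which is more conservative: 99.2% coverage at 0.90 and 98.4% at 0.95). The same method may be used for the recruitment rate so that one sentence covers both; it makes almost no difference there.

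The cost is one phrase of wording, with no extra infants and no design change. The stated lower limit becomes somewhat less favourable, for example 74.4% instead of 79.3% at 27/30.

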### Ethical and safety considerations

This study was approved by the Neonatal Research Committee at McMaster Children’s Hospital, Hamilton Integrated Research Ethics Board (14–575), and Health Canada (9427-M1133-53C). All parents or guardians will provide written and informed consent prior to enrollment.

We have established a Data Safety and Monitoring Board (DSMB) for the pilot study, which consists of two neonatologists and one pediatric surgeon. This group will meet after the first five participants are randomized and then once every 3 months until the pilot study is complete. The DSMB will review safety outcomes (i.e., treatment-related adverse events) and can request unblinding should the need arise. Unblinding will be facilitated by the unblinded research assistant who performed sequence generation and is not otherwise involved in the administration of this study. The principal investigator, co-investigators, and research assistant will remain blinded.

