**Methods/design:**

This protocol is for an external pilot study that will assess the feasibility of a superiority, placebo-controlled, parallel-design, multicenter randomized controlled trial. Participants are premature infants treated in a level 3 NICU with a gestational age 24 to 32 weeks and/or birth weight of 500 to 1500 g. Thirty participants will be recruited as part of this external pilot study. Participants will be randomized to glycerin suppository (250 mg) or placebo starting 48 to 72 h after birth and continuing once daily until meconium evacuation is complete or for a maximum of 12 days. The placebo consists of a 250-mg glycerin suppository placed in the diaper rather than the rectum. Study treatments are administered by the charge nurse on duty who is not otherwise involved in patient care. All other clinicians and research personnel will remain blinded. Outcomes for the pilot study are percentage of eligible participants randomized, percentage of infants reaching full enteral feeds, cost, and treatment-related adverse events (rectal bleeding, rectal perforation, and anal fissure).

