We recently conducted a systematic review on the use of glycerin suppositories and enemas in premature infants [17]. We identified a total of 185 infants from three single-center, randomized controlled trials [14–16]. These studies focused on the prophylactic use of glycerin suppositories (two trials) or enemas (one trial). Across all three trials, there were no differences in terms of meconium evacuation, transition to full enteral feeding, or mortality. There were no reports of rectal bleeding or perforation, but meta-analyzed data revealed a non-significant trend towards increased risk of NEC with active treatment. We concluded that going trials should be carefully monitored and stopped if it becomes clear that this trend is a real effect and not just a spurious correlation.

The results of our systematic review were complicated by the fact that all three trials were underpowered and affected by one or more major methodological issues. As a result, the quality of evidence was low to very low. We concluded that the evidence for the use of glycerin suppositories or enemas in premature infants is inconclusive and that further research is required. As a result, we designed an external pilot study to assess the feasibility of a multicenter randomized controlled trial of prophylactic glycerin suppositories in premature infants.

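### The pilot's safety outcomes and the DSMB review are defined as three rectal events, which leaves out NEC and death although the Background calls for NEC to be watched

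*Protocol article*

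**What the plan says.** **DSMB remit.** Under Ethical and safety considerations: "The DSMB will review safety outcomes (i.e., treatment-related adverse events) and can request unblinding should the need arise". The board meets after five infants are randomized and every 3 months after that.

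**Pilot outcomes.** The Outcomes section makes the same equation in the other direction: it lists treatment-related adverse events as a pilot outcome and glosses them as the safety outcomes.

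**What the term covers.** The Abstract lists "treatment-related adverse events (rectal bleeding, rectal perforation, and anal fissure". Duration of treatment stops the intervention for "clinical deterioration (vasopressors, prostaglandins, culture-proven sepsis, NEC, or death) or treatment-related adverse events (rectal bleeding, rectal perforation, or anal fissure". That sentence puts NEC and death in one class and the three rectal events in the other.

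**Where NEC and death appear as outcomes.** Only in the Outcomes paragraph on the multicenter trial, whose secondary outcomes include "days of parenteral nutrition, incidence of NEC, incidence of line sepsis" and, at the end of the list, mortality.

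**Reporting as events occur.** Under Follow-up, nurses submit possible adverse events to the research assistant: "These include any cases of rectal bleeding, rectal perforation, and anal fissure". The research assistant also checks for adverse events at least weekly.

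**The earlier signal.** The Background says "meta-analyzed data revealed a non-significant trend towards increased risk of NEC with active treatment", and then: "We concluded that going trials should be carefully monitored and stopped if it becomes clear that this trend is a real effect".

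**The concern.** The Background names one harm for which earlier data lean against active treatment, and asks that trials watch for it. The operative sections then define safety in a way that excludes that harm. A board that followed the text literally would review three rectal events, none of which was reported in the three earlier trials (185 infants in total), and would not be given counts of NEC or death.

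At stake is oversight of very vulnerable infants. Thirty infants will not settle whether the trend is real, but pilot counts carry forward into the multicenter trial. A board asked to support continuation should have seen them.

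**Working it through.** The article states no figure on this point that could be reproduced, so the check is mainly a reading of the text, with an illustration of how likely events are.

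**Step 1: follow the definitions.**
- Ethical and safety considerations: DSMB review = safety outcomes = treatment-related adverse events, joined by i.e.
- Outcomes: treatment-related adverse events = safety outcomes, again joined by i.e.
- Abstract and Duration of treatment: treatment-related adverse events = rectal bleeding, rectal perforation, anal fissure.
- Duration of treatment: NEC and death belong to the other class.

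Substituting, the stated DSMB review is the three rectal events. NEC and death fall outside it by definition.

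**Step 2: look for another route to the board.**
- Statistical analysis reports adverse events related to the intervention, so it does not bring NEC or death in.
- The stopping rule acts on one infant at a time and only during treatment, which ends by day 14 of life at the latest (Interventions). It yields no aggregate review, and later NEC would not trigger it.
- The nursing list under Follow-up is introduced by the word include, so it is open, but it names neither NEC nor death.
- Chart extraction comes at discharge, 40 weeks corrected age or death. Potential pitfalls says infants stay in hospital until 37 weeks corrected age. A survivor born at 24 weeks would therefore be extracted no sooner than 37 − 24 = 13 weeks after birth, about one whole interval between board meetings in a 6-month recruitment period.

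No section expressly sends NEC or death to the DSMB.

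**Step 3: how likely is an event in the pilot?** Sample size: n = 30, 15 per arm. The article gives no NEC rate, so the risks p below are assumptions, taken as equal and independent across infants. P(at least one) = 1 − (1 − p)^30; expected cases per arm = 15p.

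| Assumed risk p | 1 − (1 − p)^30 | P(at least one) | Expected per arm |
|---|---|---|---|
| 1% | 1 − 0.740 | 26% | 0.15 |
| 2% | 1 − 0.545 | 45% | 0.30 |
| 3% | 1 − 0.401 | 60% | 0.45 |
| 5% | 1 − 0.215 | 79% | 0.75 |
| 10% | 1 − 0.042 | 96% | 1.50 |

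For death, Potential pitfalls gives about 10% mortality in the population and expects the exclusions to remove most infants at risk. At 10%, 3.0 deaths are expected in 30 infants and P(at least one) is 96%. At an assumed 2% to 5% after exclusions, 0.6 to 1.5 deaths are expected and P(at least one) is 45% to 79%.

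**Step 4: can the pilot test the NEC trend?** Power with 15 per arm, two-sided 5% test of two proportions, normal approximation: 5% versus 10% gives 7.4%, 5% versus 15% gives 14.4%, 10% versus 20% gives 11.4%. It cannot.

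**The case against.** The other side has several good points.

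- **The nursing channel is not closed.** A reader might infer that nurses report only the three rectal events. The text does not say so: the list is open, it sits under possible rather than treatment-related adverse events, and the weekly checks carry no restriction. What stands is that NEC and death are not named, and that the DSMB sentence still limits what the board is said to review.
- **NEC and death are not ignored.** Both stop treatment in the individual infant. A death before full feeds lowers the completion rate, a pilot outcome, because all randomized infants are followed to that endpoint. Neither gives the board a count of NEC or deaths by arm.
- **The signal is weak.** The Background calls it non-significant and possibly spurious, and rates the evidence low to very low. The Discussion reports no NEC difference in two of the three trials. This limits how alarming the gap is. It does not remove the authors' own call for monitoring.
- **A charter may say more.** The article condenses a fuller protocol, and the board's clinicians (two neonatologists and a pediatric surgeon) can request unblinding. An unseen charter might widen the remit. But the article is not silent: it gives a definition, and that definition conflicts with its Background.
- **Event rates are assumed.** It is tempting to say that NEC will probably occur. At 1% or 2% the chance of any case is below one half, and the exclusions remove sicker infants, so low rates cannot be ruled out from the article.

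**Conclusion.** The point holds for the DSMB remit and the definition of pilot safety outcomes: on the article's own terms both exclude NEC and death, and this contradicts the Background. The conclusion rests on the text and does not depend on any assumed rate. The illustration, 26% to 96% for at least one NEC case over assumed risks of 1% to 10%, shows only that events are plausible enough to need a defined route to the board.

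Two stronger readings are not supported. One is that by-arm counts in this pilot could show whether the NEC trend is real: with at most 1.5 expected cases per arm over that range and power of about 7% to 14%, they could not. The other is that NEC is already fully captured, so that only wording is missing: capture after treatment ends is not shown, because the stopping rule no longer applies and Follow-up does not list the items extracted.

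This should be fixed. For a 30-infant feasibility pilot with a board in place, it does not call the design into question.

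**What to change.** - In Outcomes and in Ethical and safety considerations, define the pilot safety outcomes and the DSMB review as rectal bleeding, rectal perforation, anal fissure, NEC and all-cause death, with counts available to the board by coded arm.
- In Follow-up, name NEC and death among the events reported as they occur, and state that this runs to the end of follow-up, not just to the end of study treatment.
- Let the safety sentence in Statistical analysis refer to the same definition.

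How the counts are displayed, including whether intervals are shown for so few events, can be left to the board.

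The cost is small: a wording change in these sections, plus prompt reporting of a few more events instead of reliance on chart extraction at discharge. Dose, eligibility, the rules for individual infants and blinding of the investigators are unchanged.
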